|                           | 2b | WHO Trial Registration Data Set 
 
Primary Registry and Trial Identifying Number:
ClinicalTrials.gov, NCT06501729.
 
Date of Registration in Primary Registry:
[Insert registration date]
 
Secondary Identifying Numbers:
Not applicable.
 
Source(s) of Monetary or Material Support:
Universidad Católica de Santiago de Guayaquil.
 
Primary Sponsor:
Universidad Católica de Santiago de Guayaquil.
 
Contact for Public Queries:
Name: [name] [name]
Email: [Insert email]
Phone: [Insert phone number]
 
Contact for Scientific Queries:
Same as above.
 
Public Title:
Potential Protective Effect of Kissing on Salivary pH Recovery After Acidic Beverage Consumption.
 
Scientific Title:
Potential Protective Effect of Buccal Kissing Between Two People on the Reduction of Salivary pH.
 
Countries of Recruitment:
Ecuador.
 
Health Condition(s) or Problem(s) Studied:
Salivary pH restoration, prevention of dental caries.
 
Intervention(s): 
 
Experimental group: Kissing intervention after acidic beverage consumption.
 
Control group: No kissing after acidic beverage consumption.
 
 
 
Key Inclusion and Exclusion Criteria: 
 
Inclusion: Participants aged 18-28, good oral health, availability of a partner.
 
Exclusion: Systemic diseases affecting salivary pH, medications altering salivary pH, severe oral pathologies.
 
 
 
Study Type:
Interventional.
 
Date of First Enrollment:
march 2025
 
Target Sample Size:
45 couples (15 per group).
 
Recruitment Status:
Not yet recruiting
 
 |

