|               |     | 
 
○ Anticholinergics: e.g., atropine.
 
 
3. Presence of oral abscesses or other severe dental conditions.
 
Justification:
These criteria were selected to minimize confounding factors that could alter salivary pH, such as systemic diseases, abscesses, or the influence of medications. The age range of 18 to 28 years was chosen to reduce the likelihood of undiagnosed chronic systemic diseases, as no specific tests will be conducted to confirm their absence; participant responses will be accepted as valid. Additionally, requiring participants to already have a romantic partner ensures that the study is conducted ethically and avoids potential discomfort from pairing participants with strangers.
 
Sociodemographic Characteristics:
Participants must reside in Guayaquil, specifically near the Universidad Católica de Santiago de Guayaquil, to facilitate travel and ensure availability for multiple appointments.
 
Sample Size:
The study aims to recruit a minimum of 15 couples per group, accounting for potential dropouts. This number was determined based on a sampling of means and a reference from a similar study.
 
Selection Process:
The recruitment process will involve an open call via social media platforms targeting university students, although being a student is not an inclusion criterion. Flyers with a QR code and a registration link will direct interested individuals to a Google Form where they will provide initial data. Eligible participants will be contacted to schedule an oral health assessment and complete a health questionnaire to confirm compliance with the inclusion criteria.
                     |

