| Outcomes | 12  | 
Primary Outcome:
 
The primary outcome of this study is the time required for salivary pH to return to neutral levels (pH ~7) after the intervention (kissing). The objective is to demonstrate that the act of kissing facilitates a faster restoration of salivary pH compared to the physiological time required in the absence of a kiss.
 
Secondary Outcomes:
 
 
1. The salivary pH level measured at each time interval during the 40-minute observation period.
 
2. Comparison of salivary pH restoration rates between: 
 
o The control group and the two experimental groups.
 
o Experimental group 1 (only one partner consumes the acidic beverage) and experimental group 2 (both partners consume the acidic beverage).
 
 
 
 
Methods of Measurement:
 
A pH meter will be used to measure the hydrogen ion activity in the saliva, reflecting its acidity or basicity. The device employs a Toledo micro combined pH electrode with the following specifications:
 
 
o Measuring range: pH 0 - 14.
 
o Temperature range: 0°C - 80°C.
 
o Shaft dimensions: 60mm length and 3mm diameter.
 
o Glass membrane: U-type with resistance <600M at 25°C.
 
o Reference system: ARGENTHAL with Ag+ ion trap.
 
 
The saliva sample will be unstimulated to avoid pH alterations caused by increased salivary flow. A small sample volume is expected, and the thin electrode design ensures accurate measurement even in reduced quantities.
 
Measurement Timeline:
 
 
1. A baseline saliva sample will be collected before the participants consume the acidic beverage.
 
2. Immediately after ingesting the beverage, a second saliva sample will be collected.
 
3. Participants in the experimental groups will kiss for 40 seconds, while the control group will wait.
 
4. A saliva sample will be collected at 5-minute intervals for the next 40 minutes, resulting in a total of nine post-intervention samples per participant.
 
 
Justification:
 
Measuring salivary pH every 5 minutes is a standard approach in similar studies assessing the dynamics of salivary pH restoration. Additionally, measuring pH immediately after consuming acidic beverages is consistent with other research protocols. Using a pH meter ensures precise and objective measurements, while collecting unstimulated saliva minimizes alterations in pH caused by increased flow rate, enhancing the reliability of the data.
 |

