| Sample size          | 14 | 
The sample size calculation was conducted using the G*Power statistical software (version 3.1.9.7, Fran Faul, Universität Kiel, Germany). The calculation was based on data obtained from the pilot study titled "Comparison of Salivary pH Changes after Consumption of Two Sweetened Malaysian Local Drinks among Individuals with Low Caries Experience: A Pilot Study". This study measured salivary pH changes after consuming acidic beverages and provided the necessary statistical parameters for sample size estimation.
 
Specifically, the following values from the pilot study were used:
 
 
Control group (mineral water): mean = 7.10, SD = 0.18.
 
Experimental group (local drink): mean = 6.86, SD = 0.18.
 
 
To calculate the effect size (<math>f</math>) for ANOVA, the means and standard deviations were combined using the formula:
 $n = \frac{(2 * (Z\beta + Z\alpha)^2 * \sigma^2)}{\Delta^2}$ 
Given the mean difference (7.10 - 6.86 = 0.24) and pooled SD of 0.18, <math>d=1.33d=1.33d=1.33</math>. Dividing by the square root of the number of groups (<math>k=3</math>), the resulting effect size was <math>f=0.76</math>, which is considered a large effect size.
 
The following input parameters were used in G*Power:
 
 
Effect size (<math>f</math>): 0.76 (large effect size based on observed data).
 
Alpha error probability (<math>\alpha</math>): 0.05.
 
Power (1-<math>\beta</math>): 0.95.
 
Number of groups: 3.
 
 
The output indicated that a total sample size of 30 participants is required to achieve a power of 95%, with 10 participants per group. To account for potential dropouts, an additional 20% will be recruited, resulting in a total of 36 participants (12 per group).
 
This effect size and resulting sample size are justified based on the observed differences in the pilot study, which measured salivary pH using similar methods (pH meter, unstimulated saliva samples in test tubes) and reported statistically significant differences between groups. Using this approach ensures that the sample size is both statistically adequate and logistically feasible for this study.
 |

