| Allocation:
Sequence generation          | 16a | 
In this study, participants will be randomly assigned to one of three groups using the services of RANDOM.ORG, a reputable platform that generates true random numbers based on atmospheric noise .
 
Sequence Generation:
An external collaborator, [name] from Miami, USA, will generate the allocation sequence. She will utilize the List Randomizer feature on RANDOM.ORG, which allows users to input a list of items (in this case, unique participant codes) and receive the list back in a randomized order. This method ensures that each participant has an equal chance of being assigned to any of the three groups. Random.org
                                                                                                                                                                                                                                                                                                  |
| Allocation concealment mechanism            | 16b | 
Allocation Concealment Mechanism:
To prevent bias, the allocation sequence will be concealed from both participants and primary investigators. [name], who is not involved in the study and unaware of participant identities, will handle the randomization process. She will assign each unique participant code to a group and communicate these assignments confidentially to a designated coordinator. Participants will remain unaware of their group assignments to mitigate any anticipatory effects, such as increased salivation due to expectations.
                                                                                                                                                                                                                                                                                                                                                                                                                                   |

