| Implementation                              | 16c | 
Implementation:
During enrollment, each participant pair will receive a unique code. These codes will be sent to [name], who will perform the randomization without access to any identifying information, ensuring impartiality. She will then relay the group assignments back to the study coordinator, who will oversee the implementation during the intervention phase. This process maintains the integrity of the randomization and minimizes potential biases.
                                                                                                                                                                                                                                                                                                                                                                                                                                                                                                                           |
| Blinding (masking)                          | 17a | 
Who Will Be Blinded:
This study will incorporate blinding at three levels to minimize bias and ensure the integrity of the results:
 
 
1. Participants: Participants will remain unaware of their group assignment (control or experimental) until the day of the experiment. This approach prevents anticipatory salivation or behavioral changes that could influence the results.
 
2. Investigators: The research team responsible for collecting and analyzing the data will not know the group assignments during the intervention phase. The assignments will only be revealed after data collection is complete to avoid any unintentional biases.
 
3. External Randomizer ([name]): [name], who performs the randomization process in Miami, USA, will be blinded to participant identities. She will only receive anonymized participant codes for allocation, ensuring impartiality in group assignments.
 
 |

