| Statistical methods | 20a | 
Analysis of Primary and Secondary Outcomes:
 
The primary outcome, the time required for salivary pH to return to neutral (pH 7.0), will be analyzed using appropriate statistical methods depending on the data distribution. First, tests of normality (e.g., Shapiro-Wilk test) will be conducted to determine if the data follows a normal distribution. If the data meets the assumptions for parametric tests, a one-way ANOVA will be used to compare the mean recovery times across the three groups: control, experimental group 1 (only one partner drinks the acidic beverage), and experimental group 2 (both partners drink the acidic beverage).
 
If the assumptions for ANOVA are not met, the non-parametric Kruskal-Wallis test will be applied to compare the groups. Post-hoc analyses (e.g., Tukey's HSD for ANOVA or pairwise comparisons with Bonferroni correction for Kruskal-Wallis) will be conducted to identify specific group differences.
 
For secondary outcomes, including salivary pH levels at specific time intervals, repeated-measures ANOVA will be used if the data meets parametric assumptions. Otherwise, the Friedman test will be employed to evaluate changes in pH over time within and between groups.
 
Additionally, pairwise comparisons will be performed to assess the differences in mean recovery times between the control group and each experimental group (control vs. experimental 1, and control vs.
                                                                                                                                                                                                                                                                                                                                                                                                                                                                                                                                                                                                                                                                  |

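### Couples are randomised, but the trial is sized, measured and tested by participant: the targets of 45 couples and 36 participants are not reconciled, and the partner to be analysed is undefined

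*Protocol*

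**What the plan says.** **Allocation.** Item 16c makes the couple the coded unit: "During enrollment, each participant pair will receive a unique code", and those codes go to the randomiser. Item 16a describes a list of participant codes and adds: "This method ensures that each participant has an equal chance of being assigned to any of the three groups".

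**Target.** Item 2b gives "45 couples (15 per group". Item 10 repeats a minimum of "15 couples per group" and says that this allows for dropouts. Item 14 derives 30 participants, 10 per group, adds 20% for dropouts and arrives at "36 participants (12 per group".

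**Measurement and analysis.** Item 12 counts samples by person, "resulting in a total of nine post-intervention samples per participant", and item 20b admits to the primary analysis the participants with complete primary-outcome data. Item 20a compares recovery times by one-way ANOVA or Kruskal-Wallis, with independent t-tests or Mann-Whitney tests for the pairwise comparisons. The groups compared include "experimental group 2 (both partners drink the acidic beverage". In Experimental group 1 one partner drinks, and item 11a describes control with a single drinker.

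**The concern.** In a trial of kissing, both partners necessarily receive the same allocation, and the intervention itself mixes their saliva. Two recovery times from one couple are therefore unlikely to be independent, whereas every test named in item 20a and the calculation in item 14 assume that the units are.

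Two things are at stake. First, the enrolment target and the power claim cannot be interpreted until the counted unit is fixed. Second, Experimental group 2 has two possible values per couple where the other groups have one, and the protocol has no index partner, couple mean or couple effect to deal with this. It also does not say who drinks where only one partner does. Unless settled in advance, the choice of which value to analyse could be made after the data are seen.

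**Working it through.** **Inputs.** From item 14: f = 0.76, alpha 0.05, power 0.95, three groups, 20% added for dropouts. From items 2b and 10: 15 couples per group, 45 in all. From items 8, 11a and 20a: two drinkers per couple in Experimental group 2, one in Experimental group 1, one in control (read from the singular in 11a). The within-couple correlation (rho) is not given; values from 0 to 0.8 are assumed. The effect size is taken as stated; whether it is well derived is a separate question.

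**Step 1: reproduce item 14.** For a one-way ANOVA on N independent units, power is the probability that a noncentral F with 2 and N - 3 degrees of freedom and noncentrality N × f² exceeds the 5% critical value. Here f² = 0.76² = 0.5776. At N = 30 the noncentrality is 30 × 0.5776 = 17.33 and power is 95.0%, so 10 per group reproduces. The dropout addition also reproduces: 30 × 1.2 = 36. Both figures are counts of independent units.

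**Step 2: read the targets in couples, with one analysed value per couple.**

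| Reading | Couples | N × f² | Power |
|---|---|---|---|
| Requirement before dropout | 30 | 17.33 | 95.0% |
| 36 units are 36 couples | 36 | 20.79 | 98.0% |
| Target in items 2b and 10 | 45 | 25.99 | 99.5% |
| 36 participants are 18 couples (6 per group) | 18 | 10.40 | 74.3% |

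The protocol's own inputs thus require 30 couples, or 36 after the stated addition. That is 72 people, which is neither 36 participants nor 45 couples (90 people).

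**Step 3: effective size of Experimental group 2 if both drinkers are analysed.** The design effect for two values per couple is 1 + rho. With 12 couples, the 24 values are worth 24/1.3 = 18.5, 24/1.5 = 16.0 and 24/1.8 = 13.3 independent values at rho = 0.3, 0.5 and 0.8.

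**Step 4: type I error in that case.** The simulation used 40,000 runs per setting, normal data with equal variance and no true effect. Control and Experimental group 1 had one value per couple, Experimental group 2 had two values with correlation rho, and the test was an ordinary one-way ANOVA at a nominal 5%.

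| rho (assumed) | 12 couples per group | 15 couples per group |
|---|---|---|
| 0 | 5.0% | 5.0% |
| 0.3 | 6.1% | 6.1% |
| 0.5 | 6.9% | 7.2% |
| 0.8 | 8.7% | 8.8% |

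The t-test of control against Experimental group 2 behaves alike: 6.0%, 7.1% and 8.5% at rho = 0.3, 0.5 and 0.8 with 12 couples per group.

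**The case against.** The strongest reply is that the protocol nowhere says that both Experimental group 2 drinkers enter the primary test. Item 20a names no unit and no count, item 12 only fixes how many samples each person gives, and item 14 plans equal groups, which fits one value per couple better than an n, n, 2n layout. This stands, so the inflation in step 4 is conditional. It does not dispose of the point: items 12 and 20b work by participant and no rule selects a partner.

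Four stronger readings are tempting, and the text does not carry them.

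- Counting both partners in all three groups would give type I error of about 10%, 14% and 20% at the same correlations. Those figures do not apply: in Experimental group 1 only one partner drinks, and control is described with one drinker.
- Setting 36 participants against 90 people suggests a 2.5-fold gap. That is not like for like, because the 90 include partners who do not drink. With one value per couple, the comparison is 36 with 45.
- Item 16a might be taken to let partners land in different groups. Item 16c makes pair codes the more natural reading, so this is contradictory wording that needs correcting.
- One might infer that the drinker is chosen non-randomly or that one sex will dominate. The protocol is silent on both.

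A separate analysis plan could define the analysed partner. The allocation unit and the target, however, are protocol matters and are already stated in conflicting terms, and a couple-level model there would depart from the tests fixed in item 20a.

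**Conclusion.** The point holds in two parts of different strength. The contradiction over unit and target is explicit: the couple is coded for randomisation, but participants are said to be allocated and counted, and the targets are not linked. Depending on the reading, power at the protocol's own f = 0.76 runs from 74.3% to 99.5%. No text states the 18-couple reading, but none excludes it.

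The analysis-unit part is a gap with a conditional consequence. If both Experimental group 2 drinkers are treated as independent, true type I error is roughly 6% to 9% instead of 5%, a modest inflation. That range rests on assumed correlations of 0.3 to 0.8 and on continuous normal data, whereas recovery is observed every 5 minutes up to 40 minutes. If one partner per couple is analysed, the inflation disappears, but the conflict of targets remains and the partner still has to be named in advance. Both parts should be settled before the allocation list is drawn; item 2b lists recruitment as not yet begun.

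**What to change.** 1. **Item 16a:** state that pair codes are randomised, in line with 16c.
2. **Item 14:** state that the calculation counts couples with one analysed value each (30, or 36 after the 20% addition), and give a single target in couples that agrees with items 2b and 10. If 45 couples is kept, say that it exceeds the 36 required.
3. **Items 16 and 11a:** have the randomiser draw one index partner per couple, in all three groups, before the group is revealed. Where only one partner drinks, the index partner is the drinker.
4. **Items 20a and 20b:** base the primary analysis and its complete-case rule on the index partner. Let the second Experimental group 2 drinker enter only through a model with a random effect for couple, or with cluster-robust standard errors.

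The cost is one extra random draw per couple and a protocol amendment, which under item 25 needs ethics committee approval and a registry update. The second drinkers in Experimental group 2 will add little to the primary test.

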| Trial design                                              | 8  | 
The study will be a randomized controlled trial with parallel groups. Participants will be randomly assigned to one of three groups:
 
 
○ Control group: Participants who do not kiss after consuming an acidic beverage.
 
○ Experimental group 1: One member of the couple consumes an acidic beverage, and both partners kiss for 40 seconds.
 
○ Experimental group 2: Both members of the couple consume an acidic beverage and kiss for 40 seconds.
 
 
The results will be used to evaluate whether the act of kissing restores salivary pH more quickly than the time it takes for the body to do so physiologically. This design allows for clear comparisons of the effects of the different conditions, with an appropriate control group.
                                                                                                                                                                                                                                                                                                                                               |
| Methods: Participants, interventions, and outcomes |    |                                                                                                                                                                                                                                                                                                                                                                                                                                                                                                                                                                                                                                                                                                                                                                                                                                                                                                                                                                                                                                                                                                                                                                                                        |

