|  |     | 
for the 40-second duration. Once the timer concludes, participants will be asked to leave the cubicle and provide their saliva sample.
 
 
○ Tools and Equipment: 
 
○ Screens (biombos) to provide privacy.
 
○ Timers or stopwatches to ensure accurate intervention durations and sample collection intervals.
 
○ A calibrated pH meter to measure salivary pH.
 
○ Eppendorf tubes (3ml) for saliva collection, suitable for accommodating the electrode of the pH meter and ensuring accurate measurements.
 
 
 
 
Monitoring and Compliance:
To respect participants' privacy, researchers will not remain present during the kiss. However, they will ensure the proper initiation of the intervention and verify compliance with the protocol. Saliva collection and pH measurement will be monitored closely to ensure adherence to the timeline.
 
Justification of the Intervention:
The kiss was chosen as the intervention due to its widespread and accessible nature. Demonstrating that kissing can act as a protective factor against the reduction of salivary pH—and potentially against dental caries—could contribute positively to preventive strategies for oral health. The study aims to explore the physiological impact of kissing in a controlled and measurable manner.
 
Materials and Equipment Used:
 
 
1. Eppendorf tubes (3ml): These will collect unstimulated saliva and accommodate the pH meter electrode, as only minimal saliva is expected per sample.
 
2. Calibrated pH meter: This device will measure salivary pH with precision.
 
3. Screens (biombos): To ensure the privacy and comfort of participants during the intervention.
 
4. Timers/Stopwatches: To accurately measure the duration of the kiss and sample collection intervals.
 
 
Safety and Monitoring Measures:
The intervention (kissing) is considered a safe and low-risk activity, especially as it will involve habitual partners. The clinic, located within the university, operates with official permits and adheres to national and international standards for disinfection and biosecurity. The privacy provided by screens further enhances participant comfort. In the unlikely event of an unforeseen incident, the university's medical department will be on standby to provide immediate assistance.
 |

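### Serial pH is analysed by repeated-measures ANOVA or Friedman according to assumption checks, with nothing on sphericity; one prespecified mixed model would serve better

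*Protocol*

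**What the plan says.** Section 8 (Trial design) sets up three parallel groups: "Participants will be randomly assigned to one of three groups". Section 12 (Outcomes) lists pH at each time point as a secondary outcome, together with comparisons of restoration rates between control and each experimental group and between the two experimental groups. Samples are taken every five minutes for 40 minutes, "resulting in a total of nine post-intervention samples per participant".

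Section 20a (Statistical methods) makes the analysis of these readings conditional: "repeated-measures ANOVA will be used if the data meets parametric assumptions". It continues: "Otherwise, the Friedman test will be employed to evaluate changes in pH over time within and between groups". The one check that it names comes earlier in the section, in the text on the primary outcome: "tests of normality (e.g., Shapiro-Wilk test) will be conducted to determine if the data follows a normal distribution". It does not mention sphericity, an epsilon correction or a within-person covariance. It also does not say what is tested for normality: raw values or residuals, by cell, by time point or pooled.

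Section 20b words its complete-case rule for the primary outcome. Multiple imputation is a sensitivity analysis, to be run if more than 10% of the data are missing. Section 11a, in describing the tubes, notes that "only minimal saliva is expected per sample".

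**The concern.** There are three weaknesses in the stated rule.

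1. **Sphericity.** The time and group-by-time F tests of a repeated-measures ANOVA need equal variances of all pairwise differences between time points. On a curve recovering from an acid drop, neighbouring readings should agree more closely than distant ones, and people differ in depth and speed of recovery. Sphericity is therefore unlikely, and an uncorrected group-by-time test would reject too often. If sphericity does count among the parametric assumptions, the same rule would tend to send the analysis to Friedman.
2. **Choice by test.** A method picked by an assumption test can change by chance. Here the change matters, because the Friedman test ranks readings within a person. It does not provide the between-group comparison that section 12 asks for, although section 20a assigns it that role.
3. **Missing readings.** Classical repeated-measures ANOVA needs every reading from every person, so one unusable sample removes that person from this analysis.

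At stake is the comparison of recovery curves between groups: its error rate, its sample, and whether it is made at all.

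**Working it through.** **Inputs from the protocol.** Groups k = 3 (section 8). Post-intervention readings T = 9 (section 12). From section 14: "Alpha error probability" 0.05, effect size f = 0.76, and 10 participants per group, or 12 after the 20% addition. Section 10 gives 15 couples per group. I therefore used n = 10, 12 and 15.

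**Inputs assumed.** The correlation between readings, the share of unusable tubes, and the unit on which normality is tested. The protocol gives none of these.

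**The plan's own figure.** The protocol states no error rate for the repeated-measures test. Its one related calculation is the total of 30, which by section 14 "is required to achieve a power of 95"%. With λ = N·f² = 30 × 0.76² = 17.3, the one-way ANOVA has power 0.9501; N = 27 gives 0.923. So 30 is reproduced, and 30 × 1.2 = 36. This serves here only to fix the group sizes.

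**Step 1: error rate of the group-by-time test.** The test has (k−1)(T−1) = 2 × 8 = 16 and (N−k)(T−1) degrees of freedom; at N = 36 the second is 33 × 8 = 264. Greenhouse-Geisser multiplies both by an epsilon of at most 1. I simulated 20,000 trials per setting with normal data, independent persons and no group effect. Ranges are over n = 10, 12 and 15.

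| Assumed correlation | Epsilon | Uncorrected | Greenhouse-Geisser |
|---|---|---|---|
| Compound symmetry 0.5 | 1.000 | 5.0-5.1% | 3.2-3.6% |
| AR(1) 0.3 | 0.877 | 5.6-6.0% | 3.4-3.7% |
| AR(1) 0.5 | 0.705 | 7.5-8.0% | 4.2-4.5% |
| AR(1) 0.7 | 0.521 | 10.1-10.3% | 4.7-5.1% |
| AR(1) 0.8 | 0.437 | 11.2-11.5% | 4.8-5.1% |
| AR(1) 0.9 | 0.362 | 12.7-12.9% | 5.0-5.2% |

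Adding a person random intercept to AR(1) changes little: 7.6-8.0% at 0.5 and 11.5-11.8% at 0.8, uncorrected. The group main effect compares each person's mean over the nine readings, so it does not need sphericity.

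**Step 2: chance switching.** Shapiro-Wilk at 5% was applied to exactly normal data, with 1,000 trials per setting and any single failure triggering the switch.

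- All 3 × 9 = 27 group-by-time cells: 1 − 0.95²⁷ = 75% if independent; 63-77% simulated.
- Residuals at each of nine times: 1 − 0.95⁹ = 37% if independent; 28-39% simulated.
- One test of all pooled residuals: about 5-14% for AR(1) up to 0.7, about 23-26% at 0.8, about 48-50% at 0.9, and about 53-55% under compound symmetry 0.8.

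The span is thus about 5% to 77%, set mainly by a choice that the protocol leaves open.

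**Step 3: persons lost to missing readings.** If each tube fails independently with probability p, the share of people lacking at least one of nine readings is 1 − (1 − p)⁹.

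- p = 1%: 1 − 0.99⁹ = 8.6%
- p = 2%: 1 − 0.98⁹ = 16.6%
- p = 5%: 1 − 0.95⁹ = 37.0%

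If the 10% trigger in section 20b counts readings, none of these rates reaches it, even where 37% of people would be dropped.

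**The case against.** The strongest reply is that a sphericity correction, the unit of normality testing and the handling of missing secondary readings usually belong in a statistical analysis plan, which is not at hand. Section 20a does not say that the test will run uncorrected. That stands for the details: a Greenhouse-Geisser correction may well be planned, and it alone would repair the error rate. It does not cover the rule that section 20a does fix, namely a switch between two methods of which the second cannot answer the between-group question.

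A reader might go further than the text allows in three ways.

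- **That the test runs at 8-13%.** This needs AR(1)-type correlation of about 0.5 to 0.9 and no correction. Under compound symmetry or AR(1) 0.3 the rate is 5-6%, and the protocol gives no correlation.
- **That normality testing will trip in about 70% of trials.** This needs 27 separate cell-wise tests with any one failure decisive. The protocol describes no such scheme. It introduces its normality test for the primary outcome and speaks of parametric assumptions generally for the secondary ones.
- **That the plan excludes anyone with a lost tube.** That follows from the classical method, not from a stated rule. Section 11a mentions small volumes to explain the choice of tube, and section 12 says the thin electrode copes with them. The protocol does not predict lost readings, and the tube-loss rates are illustrative.

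The harms also do not add up. Inflation arises only when the ANOVA branch is used, and loss of the group comparison only when it is not.

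**Conclusion.** The concern holds in a limited form. Section 20a fixes a data-dependent choice for nine serial readings, does not address sphericity, and falls back on a test that does not compare groups. If the group-by-time test is uncorrected, its false-positive rate lies between about 5% and 13%, depending on an assumed correlation; corrected, it is about 3-5%. The group main effect is sound on this count. The chance of switching methods on normal data lies anywhere from about 5% to 77%, because the unit of testing is not stated. Loss of persons depends on a tube-failure rate that nobody has given. Only the secondary pH-over-time analysis is affected, so the severity is moderate to minor.

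**What to change.** In section 20a, replace the conditional choice by one prespecified linear mixed model for post-intervention pH, fitted to all available readings whatever a normality test shows:

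- fixed effects for group, time (categorical) and group-by-time, with the pre-drink and the post-drink, pre-kiss readings as covariates;
- a parsimonious serial within-person covariance, for example AR(1) plus a person random intercept. An unstructured matrix over nine times has 9 × 10 / 2 = 45 parameters, too many for about 36 people;
- a couple random effect only where both partners are measured;
- small-sample degrees of freedom.

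The error rate of this model was not simulated here.

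As a minimum, if repeated-measures ANOVA is kept, apply the Greenhouse-Geisser correction always and do not choose the method by a normality test. This minimum does not solve the loss of people with a missing reading.

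The cost is wording in section 20a and a little more analysis work. No new data are needed.
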